**Fig. 1 Fig1:**
[figure not shown]
RCT study flowchart

This trial is registered with the Clinical Trials Protocol Registration and Results System (PRS) number: NCT04517474.

### Adaptations

The first required step for this study was to translate the CANreduce program from German into Spanish and culturally adapt its contents. The process was performed by external professional bilingual translators (German-Spanish, Spanish-German). After all adaptations, all text was reviewed and discussed by four mental health professionals (three psychiatrists and a psychologist) who are faculty within the Addiction Research Group at the Hospital del Mar Medical Research Institute (IMIM). Twelve cannabis users then accessed the first version of CANreduce-SP before study launch and were asked about the online interface (readability on different devices), content (appropriate, understandable, and use of appropriate colloquial language), and program (interest and value). Due to the COVID-19 pandemic, all these issues were discussed in an online focus group. Consensual changes were later implemented on the final version of the website.

### Recruitment of study participants

Recruitment started in November 2020 and may remain open until June 2022 to ensure that the estimated required sample size of 300 participants is met. Participants will be recruited through advertisements placed in Spanish cannabis social clubs, on university premises, and on online national search engines like Google Ads. Those who complete questionnaires upon program completion (*t*_1_) will be rewarded with a digital voucher worth €15. Those who complete the follow-up questionnaires at three (*t*_2_) and six (*t*_3_) months will be reimbursed with another €15 digital voucher for each these two time points. To enhance subject retention in the study, any participant who completes all the assessments will be rewarded with an extra €15 voucher.

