### Sample size calculation

Anticipating that a Cohen’s *d* of 0.40 would be realistic to determine effect size differences on the primary outcome between groups, based on previous study experiences [23–26], a sample size of *n* = 100 in each study group would have 80% power on two-tailed *t*-test calculations performed using G*Power software (Faul, Kiel) and an alpha error of 5%. Given an average attrition rate of 50% in online studies involving cannabis misusers [26], our final adjusted sample size is *N* = 450.

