### Data analysis

All analyses will be performed on an intention-to-treat basis and verified by complete case analyses. Imputation procedures will be chosen based on missing data patterns (e.g. using the MICE multiple imputation function in the statistical software package R and between 20 and 40 imputed datasets, depending on the extent of missing data, in accordance with suggestions made by Graham [47]). Moreover, study dropout analysis will be performed comparing participants who completed the follow-up survey against those who did not. Cohen’s *d* will be determined, with the significance threshold for all analyses defined as alpha = .05. The primary outcome—number of days of cannabis use over the preceding 7 days, estimated using the Time-Line-Follow-Back method—will be analysed by means of linear regression models with baseline characteristics and group allocation as predictors. Secondary outcomes will be analysed accordingly.

Since this will be a low-risk intervention, there will be no independent data monitoring committee. Study data will be analysed by the lead and the principal investigator after completion of data acquisition. Planned analyses are described in this section. There will be no formal stopping rules since we do not anticipate problems detrimental to participants. Data collection will be stopped when at least one hundred and fifty participants will be included in each group. The lead investigator and the principal investigator will make the final decision to terminate the data collection.

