### Trial status

This trial is registered with the Clinical Trials Protocol Registration and Results System (PRS) number: NCT04517474. Registered 18 August 2020, https://clinicaltrials.gov/ct2/show/NCT04517474 (archived by archive.is https://archive.is/N1Y64). The project commenced in November 2020 and recruitment is anticipated to end by November 2022.

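### The recruitment section gives the pre-attrition total of 300 as the required sample, against 450 (150 per group) elsewhere, and the recruitment end dates also differ

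*Protocol article*

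**What the plan says.** Five places in the protocol article bear on how many participants are sought and when recruitment ends.

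- **Recruitment of study participants:** recruitment began in November 2020 and "may remain open until June 2022 to ensure that the estimated required sample size of 300 participants is met".
- **Sample size calculation:** a Cohen's d "of 0.40 would be realistic to determine effect size differences on the primary outcome between groups"; "100 in each study group would have 80% power on two-tailed" t-tests at 5% alpha; then "Given an average attrition rate of 50% in online studies involving cannabis misusers", "our final adjusted sample size is *N* = 450".
- **Data analysis:** "Data collection will be stopped when at least one hundred and fifty participants will be included in each group". The same paragraph leaves the final decision to end data collection to the lead and principal investigators.
- **Abstract (Trial registration) and Trial status:** both state that "recruitment is anticipated to end by November 2022".

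Allocation is 1:1:1 (Randomization and trial flow), so 150 per group is 450 in total.

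**The concern.** The number called required in the recruitment section is two thirds of the number that the sample-size section adopts. It matches the total needed before attrition, so a figure for analysable participants appears to have been carried over as a recruitment target. The same sentence also gives an end date five months before the one stated elsewhere.

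What is at stake is the attrition allowance. The plan expects to lose half of its participants and lists high dropout among its limitations. A team working from the recruitment section alone could regard the target as met at 300, with no allowance left for those losses. A null result, particularly for the comparison of the two active arms, would then be hard to interpret.

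**Working it through.** **Inputs, all from Sample size calculation:** d = 0.40; two-sided alpha 5%; target power 80%; 100 per group; attrition 50%; adjusted total 450. There are three groups of equal size.

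**1. Reproduce the plan's base figure.** For two means, n per group = 2(z₀.₉₇₅ + z₀.₈₀)² / d² = 2(1.960 + 0.842)² / 0.16 ≈ 98.1, so 99. The noncentral t calculation gives 99.08, rounded up to 100. Power at 100 per group is 80.4% (t-test) or 80.7% (normal approximation). The stated 100 per group and 80% are right, and 3 × 100 = 300 is the total before attrition.

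**2. Set the targets and dates side by side.**

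| Section | Total | Per group | Recruitment end |
|---|---|---|---|
| Recruitment of study participants | 300 | 100 | June 2022 |
| Sample size calculation | 450 | 150 | not given |
| Data analysis | at least 450 | at least 150 | not given |
| Abstract; Trial status | not given | not given | November 2022 |

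**3. Apply the plan's own attrition.** Power ≈ Φ(d√(n/2) − 1.96), with n the number per arm with data and attrition equal across arms. The t-test result follows each line.

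- 300 recruited: 300 × 0.5 / 3 = 50 per arm. Φ(0.40 × √25 − 1.96) = Φ(0.04) = 51.6%; t-test 50.8%. The difference detectable with 80% power is d = 0.57.
- 450 recruited: 450 × 0.5 / 3 = 75 per arm. Φ(0.40 × √37.5 − 1.96) = Φ(0.49) = 68.8%; t-test 68.2%. The difference detectable with 80% power is d = 0.46.

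**4. Check whether 450 and 300 fit together.** 450 × 0.5 = 225 with data, not 300. The two agree only if attrition is 1 − 300/450 = 33%. The figure 450 is 300 × 1.5, whereas keeping 300 with data at 50% attrition requires 300 / (1 − 0.5) = 600. So 450 cannot be explained in the text as the number that leaves 300 with outcome data.

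**The case against.** The strongest defence is that only one passage states when data collection stops. That passage is in Data analysis, and it already uses 150 per group, in agreement with the adjusted total in Sample size calculation. The recruitment sentence is permissive: it says how long recruitment may stay open, not that it closes at 300. On this view 300 is a number left without its attrition adjustment, and the two dates are both forecasts. This largely stands, and it lowers the severity. It does not remove the point, because the sentence still calls 300 the required sample and nothing corrects it.

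A kinder reading takes 300 to mean participants with outcome data. The sentence does not say so, it stands in a section on recruitment, and 450 at 50% attrition would yield 225.

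A reader might also infer two stronger things that the document does not support:

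- **That the trial as planned has 51% power.** That figure needs closure at 300, 50% attrition, observed participants only, and one unadjusted pairwise test. With complete follow-up, 300 gives about 80%. Data analysis plans multiple imputation and regression on baseline characteristics; the document gives no figures from which their effect on power could be worked out.
- **That two targets open the way to a stop guided by results.** The investigators' discretion comes from the final-decision clause in Data analysis and would exist without the recruitment sentence. No interim analysis is described, and analysis is to follow once data collection is over.

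**Conclusion.** The inconsistency is real and unreconciled: 300 against 450, and June against November 2022. The 300 is the total before attrition, presented as the required recruitment sample. Recruiting only to that number, with the plan's 50% attrition falling equally on the arms, would leave 50 per arm and about 51% power for d = 0.40, against the stated 80%, under the restrictions on the test given above.

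It should be fixed. It does not invalidate the design, because the only explicit stopping statement already carries the larger target. Nor should a reader conclude that adopting 450 throughout restores 80% power. It removes the contradiction, but at 50% attrition it gives about 68% on the same basis.

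**What to change.** 1. In Recruitment of study participants, replace 300 with the randomised target used in Sample size calculation and Data analysis: 450, that is 150 per arm. If 300 is kept anywhere, label it only as the total before the attrition allowance.
2. Give one recruitment end date in the abstract, Recruitment of study participants and Trial status.
3. Keep the per-group target in Data analysis as the single stopping criterion. Do not add a clause that closes recruitment at the target or a date, whichever comes first, since that would permit a stop below target.
4. Do not write that 450 randomised yields 300 with outcome data. In Sample size calculation, state either the power at 450 with 50% attrition (about 68%, 75 per arm) or the attrition that 450 covers while keeping 100 per arm (33%), and make the recruitment section agree with it.

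The cost is wording in a few sentences. The larger target already stands in the plan, so these edits add no participants. Raising the target above 450 to recover 80% power at 50% attrition would be a separate design decision with a real recruitment cost.

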### Registration and consent procedure

Applicants only are required to provide minimal personal data: e-mail address, phone number(s) (only if they need to be contacted to complete follow-up questionnaires), and limited primary sociodemographic data (age, gender, level of education, etc.). Registration for participation will be performed exclusively online. Before the register, each participant will be informed online about the study and will have the option to ask any questions they might have via e-mail before signing the online informed consent form. The information they will be provided is summarized in Table 1.

**Table 1 Tab1:** Information provided to participants before they provide signed informed consent

1. Purpose, background, and an overview of the study
2. Inclusion and exclusion criteria (Table 2)
3. Description of the three treatment arms^a^ and their chances of being allocated to each one of these three arms
4. Financial aspects (no participation fee, compensation for participation)
5. Potential risks of participation and when to contact their general practitioner or a professional they can select from a medical advisory and emergency service list that will always be accessible to them, merely by clicking on the site’s Help icon
6. The inability of CANreduce-SP to replace face-to-face therapy for problematic cannabis use or abuse
7. Voluntary nature of their participation and their right to withdraw at any time without consequences, except for the loss of further compensation
8. Confidentiality and data protection (anonymity is ensured by not recording real names or postal addresses and by deleting e-mail addresses and phone numbers before statistical analysis and data archiving)
9. Protocol approval was granted by the ethics committee of the IMIM Hospital del Mar d'Investigacions Mèdiques after the committee had reviewed the study: num. 2019/8901/I.

^a^No details about how the two active treatment arms differ will be provided

**Table 2 Tab2:** Inclusion and exclusion criteria and underlying rationale

**Inclusion criteria**	**Reasoning**
Informed consent via the Webform	To ensure adequate knowledge of the procedures and declare their consent
Minimal age of 18 years	To ensure a minimum age of participation
Cannabis use at least once weekly over the last 30 days	To include participants with less than daily cannabis use, increase the validity of results
At least once-weekly Internet access and a valid e-mail address	To ensure at least some access to the intervention
Good command of the Spanish language	To ensure that participants will be able to understand the information provided
**Exclusion criteria**	**Reasoning**
Participation in other psychosocial or pharmacological treatments for the reduction or cessation of cannabis use	To avoid confounding treatment effects
Current pharmacologically-treated psychiatric disease or any history of psychosis, schizophrenia, bipolar type I, substance use disorder, or significant current suicidal or homicidal thoughts	To avoid having subjects with these problems enter the study, since they could hinder the treatment’s effectiveness

Once participants have activated all checkboxes reaffirming essential study statements, they will be able to click the submit button, and informed consent will be assumed.

### Randomization and trial flow

Once participants have completed their baseline assessment (*t*_0_), they will be randomized by a computer algorithm in a 1:1:1 ratio into one of three parallel groups and will be registered automatically in the background database. Participants’ internet protocol (IP) address will be monitored to prevent multiple registrations from one user attempting to have more than a single account or be allocated to a different group than originally assigned. Participants assigned to the control condition (TAU/study arm 3) will be remitted to a list with the treatment centres nearest their postal code. After 3 months in TAU, participants will gain access to CANreduce-SP without psychological support. The four assessment points of the study are depicted in Fig. 1. All subjects will be asked about their potential for using some different treatment during their participation in the study. A reminder e-mail will be sent before each assessment. It will contain information about the value of their answers, the estimated length of the questionnaire (in time to complete), and compensation for each evaluation to enhance the response rate. The same e-mail will be sent if there is no answer within 2 days and again after 4 days. One week after the last e-mail, participants will be contacted by phone and will be offered the option of completing the follow-up questionnaire verbally with an interviewer. Participants who drop out will be asked to answer a few questions pertaining to the two the primary outcomes and why they have decided not to continue in the study. Inactivity will not be considered a dropout criterion, due to the breaks that participants of web-based interventions commonly take. It is expected that some of these users will re-join the program later. A participant’s active withdrawal from the study will be the only dropout criteria. If possible, all data already gathered from these participants will be analysed. Figure 1 depicts the flow of subjects through the study.

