### Composition of the coordinating centre and trial steering committee

The steering committee consisting of all lead and principal investigators of the two research centres will have virtual meetings to address goals and progress of the project monthly for 6 months and later when needed. The lead investigator of the present RCT trial was responsible for the study design, prepared the protocol, and will organize weekly virtual or presential meetings with the trial management group. In these meetings, the trial management group will report on problems and progress of ongoing data collection. The trial management group will consist of 2 research assistants (psychologist) responsible for Google Ads review, who will answer to the participants’ emails (general questions or psychological support), sending the SMS reminders and helping participants to fulfil the follow-up questionnaires by phone. The lead investigator together with the principal investigator will decide on trial termination and will write up study results for publication.

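### The short primary-outcome questions are stated only for participants who actively withdraw; a non-responder who declines the full questionnaire by phone has no stated short fallback

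*Protocol article*

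**What the plan says.** All of the rules on follow-up contact stand in the protocol article, under Randomization and trial flow.

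- **Short set.** "Participants who drop out will be asked to answer a few questions pertaining to the two the primary outcomes". They are also asked why they are leaving.
- **Who counts as a dropout.** "Inactivity will not be considered a dropout criterion, due to the breaks that participants of web-based interventions commonly take", and a participant's "active withdrawal from the study will be the only dropout criteria".
- **Non-responders.** A reminder goes out before each assessment and is repeated at 2 and 4 days if no reply has come. Where the e-mails fail, a call follows a week later: "participants will be contacted by phone and will be offered the option of completing the follow-up questionnaire verbally with an interviewer".

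The section on the coordinating centre and steering committee gives the research assistants the task of "sending the SMS reminders and helping participants to fulfil the follow-up questionnaires by phone". The recruitment section adds vouchers for completed follow-ups.

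The sample size section plans for loss: "Given an average attrition rate of 50% in online studies involving cannabis misusers". It gives one figure and does not separate withdrawal from non-response. The Data analysis section sets recruitment at 150 or more per group, plans an intention-to-treat analysis with imputation and a complete-case check, and adds that a "study dropout analysis will be performed comparing participants who completed the follow-up survey against those who did not".

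**The concern.** The protocol accepts that a few questions on the primary outcome are worth asking when someone will not do the whole assessment. As written, it makes that offer only to people who formally leave. Someone who stops answering without announcing a withdrawal is not a dropout under the stated criterion, and what the phone call offers is the follow-up questionnaire.

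The primary outcome is a single count of use days over the preceding 7 days. The Measurements section surrounds it with 30-day use, joints, CUDIT-R, SDS, AUDIT, two eight-item PROMIS forms and EQ-5D-5L, plus a negative-effects instrument at 3 months. A person reached by phone might give the one count and refuse the rest, and the document states no route by which that answer would be sought.

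At stake is how much of the primary outcome is observed and how much is imputed, in a trial that plans for half its participants to be lost. An analysis plan cannot recover outcomes that were never requested.

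**Working it through.** **1. Who is offered what, read literally**

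| Participant | Contact stated | Short primary-outcome set stated? |
|---|---|---|
| Actively withdraws | Asked a few questions and the reason for leaving | Yes |
| Does not answer, then completes by phone | Reminders, then call | Not needed |
| Does not answer, reached by phone, declines the questionnaire | Reminders, then call | No |
| Does not answer, never reached | Reminders, call attempted | No |

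The gap is the third row. The fourth row could be helped only by a short item sent by e-mail or SMS.

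**2. The plan's own figure**

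Inputs from the sample size section: d = 0.40, two-sided alpha 5%, power 80%, t-test. The required n is 99.08 per group, so 100, as the protocol states. Power at 100 per group is 80.4%.

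**3. Observed numbers at the stated loss**

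Inputs: 150 per arm (Data analysis) and 50% attrition (Sample size calculation). Observed per arm: 150 × 0.50 = 75. Power at 75 per arm with d = 0.40 is 68.2% (two-sample t-test, observed cases).

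**4. Illustration of a wider short form**

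The recovery of 10 to 20 percentage points is an assumption. With equal arms, the standard error of a difference is proportional to √(2/n), so its ratio to the present value is √(75/n).

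| Recovered | Observed per arm | SE ratio | SE reduction | Share missing | Power at d = 0.40 |
|---|---|---|---|---|---|
| 0 points | 75 | 1 | – | 50% | 68.2% |
| 10 points | 150 × 0.60 = 90 | √(75/90) = 0.913 | about 9% | 40% | 76.1% |
| 20 points | 150 × 0.70 = 105 | √(75/105) = 0.845 | about 15% | 30% | 82.2% |

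Ten points of 150 is 15 people, or 15/75 = 20% of those missing. Twenty points is 30 people, or 30/75 = 40%.

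**5. What share of the missing does the present rule leave out?**

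Let s be the share of the 75 missing per arm who actively withdraw. The document does not give s. The short set is offered to 75 × s and not to 75 × (1 − s).

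| s (assumed) | Offered the short set | Not offered it |
|---|---|---|
| 10% | 7.5 | 67.5 (90%) |
| 25% | 18.75 | 56.25 (75%) |
| 50% | 37.5 | 37.5 (50%) |
| 75% | 56.25 | 18.75 (25%) |

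The share left out is above one half only if s is below 50%, so it cannot be fixed from the document.

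**The case against.** The strongest objection is that the trial already has a rescue for silent non-responders, in the sentence just before the one on dropouts. They are phoned and can complete the questionnaire with an interviewer, and that questionnaire carries the primary outcome. SMS reminders and vouchers support this. A reader might infer that most people with missing data get no rescue at all, or that the 50% loss is mainly silent. The documents support neither: the call exists, and the 50% is undivided. This part of the objection stands.

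The illustration is also open to challenge. It requires 20% to 40% of the missing to answer after ignoring the e-mails, and no contact or answer rate is given. The 50% may already be net of such reminders. The standard errors are for observed cases, whereas the main analysis imputes. All of this stands, so the figures show scale and are not a forecast.

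A reader might also see a contradiction between the withdrawal-only criterion and the planned dropout analysis, which compares survey completers with non-completers. That reading is too strong. One rule says when a person has left the trial, and the other names a comparison. The shared word invites confusion, but the two can coexist.

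Finally, item order and the handling of partial phone answers may be set out in the full protocol. The document does not say that partial answers are discarded, nor that every instrument is asked at every follow-up. What remains is that the article states a data-collection rule, names who receives the short set, and does not include non-responders who decline the call's offer.

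**Conclusion.** The point holds in a narrow form. The short primary-outcome questions are tied to active withdrawal, and non-responders who decline the questionnaire by phone have no stated short fallback. This rests on the text alone.

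How many people it affects is unknown. Under the assumed 10 to 20 point recovery, observed numbers would rise from 75 to between 90 and 105 per arm, with a 9% to 15% smaller observed-case standard error. That matters because the plan's own calculation needs 100 per group, while 150 recruited at 50% loss leaves 75. Whether the people missing differ systematically from those observed is a matter of judgement that the document cannot settle.

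This is a low-cost improvement to a stated collection rule, not the repair of a missing rescue.

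**What to change.** 1. Offer the existing short set to every participant who has not returned the survey after the e-mail reminders, whether or not they have withdrawn. In the planned phone call, ask the 7-day use-days item first and then offer the rest. The same item could go out through the existing SMS or e-mail channel to those not reached.
2. Report active withdrawal separately from missing primary outcome at each time point, so that the dropout analysis is not read as an analysis of withdrawals.
3. State what the short set contains. The sentence that introduces it refers to two primary outcomes, while the Measurements and Data analysis sections name one.

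The cost is small, because the call, the staff, the SMS channel and the short set are already planned. The downside is that some people who would have completed the whole questionnaire by phone may stop after the first item, so a few secondary outcomes may be lost.
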